### Outcomes

#### Primary outcome

Outcome 1: Mean adherence to ART (Time Frame: adherence over a 12-month period continuously tracked remotely): Wisepill devices monitor the date and time of all device openings to retrieve ART medication, allowing ART adherence to be tracked continuously on the Wisepill server. Mean adherence will be coded as the number of ART doses taken / number of doses prescribed, with adherence being capped at 100% each day to avoid multiple openings on a given day artificially inflating mean adherence.

Outcome 2: The fraction of clients with adherence of 90% or more (Time Frame: continuously tracked remotely).

Outcome 3: Probability of reaching adherence target (Time Frame: tracked every 3 months corresponding to routine prize drawing opportunities). Probability that participants in the treatment groups reach their assigned target (T1), self-selected target (T2), or high fixed target of 90% (T3).

#### Secondary outcomes

Outcome 1: Fraction of clients with treatment interruptions of more than 48 h (Time Frame: Continuously tracked remotely).

Outcome 2: Suppressed viral load (viral load ≤ 200 copies/ML) among participants (Time Frame: At baseline and month 24): Viral load will be chart abstracted from clinic data. They are typically done once a year as part of routine clinical care.

Outcome 3: Retention in Care, chart abstracted from clinic data. First, we will use the binary definition of retention from the Health Resources and Services Administration HIV/AIDS Bureau as at least 2 clinic visits separated by 90 days in the previous 12 months. Second, we will use the more detailed measure outlined by Lee et al. [12] to create a variable that categorizes clients as having different levels of retention in care that provides more granular information about retention. We will define a client as fully retained in care if they attended all scheduled appointments over the previous 12 months (usually 4 or 5 total appointments). We will then create three different levels of care disengagement: missed one appointment but not more than 6 months without a visit, missed 2 appointments or 6–9 months without a visit, and missed 3 or more appointments or 9–12 months without a visit.

### Sample size and power

We have calculated the size of effects that our sample will be able to detect with 80% power (2-tailed test) with regard to outcomes at months 12 and 24, and assuming 10% attrition every year (we observed 8% attrition for our pilot study, so this is a conservative estimate). For the *primary outcome of adherence*, a sample size of 140 participants in each arm (*n* = 560 total) will be able to detect an 8-percentage point (pp) difference in mean adherence between each treatment arm and control, and compared to each other. The corresponding difference at month 24 is 9 pp. This assumes mean control group adherence of 62%, based on our pilot data. For the *secondary outcome of viral suppression*, we use a conservative estimate of about 70% of clients in the control group showing suppression based on discussions with the Mildmay team. Our sample size of 140 participants in each of the three arms will be able to detect about a 10 pp difference at month 12, and 11 pp at month 24. These represent conservative estimates of minimum detectable effect size that do not account for stratified randomization that we will perform to increase power, and to achieve better balance compared to a simple random draw [39].

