**Methods / design:**

We will enroll 628 HIV-positive youth between ages 15 and 30 into a 3-year randomized controlled trial. Participants will be randomized 1:1:1:1 to a control arm or one of three intervention arms (*n* = 157 each) that allow them to enter a prize drawing for small incentives if their ART adherence meets the given goal. In the first arm (T1, assigned subgoal), goals will be externally assigned and adapted to their initial adherence level. In the second arm (T2, participatory subgoal), participants can set their own interim goals. In the third arm (T3, fixed goal), all participants must reach the same target goal of 90% adherence. T1 and T2 participants are required to reach 90% adherence by month 12 to participate in a larger prize drawing. The control group receives the usual standard of care. All four groups will receive weekly motivational messages; the three treatment groups will additionally receive reminders of their upcoming prize drawing. Adherence will be measured continuously throughout the intervention period using electronic devices and for 12 months post-intervention. Surveys will be conducted at baseline and every 6 months. Viral loads will be measured annually. The primary outcome is Wisepill-measured adherence and a binary measure for whether the person took at least 90% of their pills. The secondary outcome is the log-transformed viral load as a continuous measure.

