### Sampling and participants

We expect to enroll 1256 individuals for the observation phase of the study that serves to measure baseline adherence. Monitoring baseline adherence will ensure that individuals being randomized to the interventions are indeed those in need of adherence support, i.e., have relatively low baseline mean adherence of less than 90%.

We arrived at this starting sample size in the following way. For the primary outcome of adherence, a sample size of 140 participants in each arm (*n* = 560 total) will be able to detect an 8 percentage point (pp) difference in mean adherence between each treatment arm and control, and compared to each other. The corresponding difference at month 24 is 9 pp. This assumes mean control group adherence of 62%. In order to reach this required sample size at year 3, we assume 6% attrition per year over 2 years of the study (1.06^2 = 1.1236) which results in a sample size for the beginning of GOALS recruitment to be 629 (560 × 1.1236). To ensure an even number across the four study arms, we reduce this target from 629 to 628. We then assume that 50% of those who complete the adherence observation phase are eligible for the GOALS intervention. We therefore need a starting sample size of 1256 ((628/50) × 100). All assumptions surrounding attrition rates and rates of adherence are based on data from PI [name]’s previous study at the same site.

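### The detectable differences quoted for viral suppression (10 pp at month 12, 11 pp at month 24) do not follow from the stated inputs, which give about 14 to 15 pp per arm versus control

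*Protocol article*

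**What the plan says.** The Sample size and power section sets out what the trial can "detect with 80% power (2-tailed test) with regard to outcomes at months 12 and 24". Its allowance for dropout is given as "assuming 10% attrition every year". For suppression it adds "we use a conservative estimate of about 70% of clients in the control group showing suppression". The number behind the claim is put as "Our sample size of 140 participants in each of the three arms", and the claim for suppression is that this number "will be able to detect about a 10 pp difference at month 12, and 11 pp at month 24". It calls these figures conservative because they take no credit for stratified randomisation. No alpha is given. The contrast (each treatment arm against control and against each other) is stated in the sentence on adherence, not in the one on suppression.

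Elsewhere the article gives a second attrition figure: in Sampling and participants, "we assume 6% attrition per year over 2 years of the study". The abstract says "We will enroll 628 HIV-positive youth between ages 15 and 30", which is 157 per arm. On the outcome itself, the abstract says "The secondary outcome is the log-transformed viral load as a continuous measure". The Secondary outcomes section instead lists binary suppression (200 copies/mL or less) at baseline and month 24.

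**The concern.** A difference of 10 pp from a 70% base, with about 140 per group, is well below what a two-group comparison of proportions usually detects at 80% power. The text offers nothing that would close the gap: no covariate gain, no pooling of arms and no relaxed alpha. By its own account it leaves out even the gain from stratification.

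Suppression is the only virological outcome in the Outcomes section and part of the year-2 objective, and the Limitations section describes the sample as well powered for clinically important effects. If the figures stand, a null result could be read as evidence against a 10 pp effect that the trial had only about an even chance of detecting.

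**Working it through.** **Inputs.** Control proportion p1 = 0.70, 80% power, two-tailed, 140 per arm, 10% attrition per year (all from Sample size and power); 157 per arm randomised (628/4). Assumed: two-sided alpha 0.05, and one arm against control at 1:1.

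**Formula** (two proportions, pooled variance under the null). With p2 = p1 + d and pbar = (p1 + p2)/2, the detectable d solves

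d = 1.960 × sqrt(2·pbar·(1 − pbar)/n) + 0.842 × sqrt((p1(1 − p1) + p2(1 − p2))/n)

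**Attempt to reproduce 10 pp at n = 140.** At the solution p2 = 0.8403, so pbar = 0.770. The first term is 0.0986 and the second 0.0417, so d = 0.140. The inputs give 14.0 pp, not 10.

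**Sample size for the stated differences.**
- 70% vs 80%: (1.960 × sqrt(0.375) + 0.842 × sqrt(0.370))² / 0.10² = 293.2, so 294 per arm.
- 70% vs 81%: (1.960 × sqrt(0.36995) + 0.842 × sqrt(0.3639))² / 0.11² = 238.8, so 239 per arm.

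**Power at 10 pp, n = 140.** (0.10 − 1.960 × sqrt(0.375/140)) / sqrt(0.370/140) = −0.028, so power is 48.9%.

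**Matched by month**, because the text leaves open whether 140 is before or after attrition:

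| Reading | n, month 12 / 24 | Detectable increase (pp) | Power for 10 pp, month 12 | Power for 11 pp, month 24 |
|---|---|---|---|---|
| 140 before 10% yearly loss (×0.9, ×0.81) | 126 / 113 | 14.7 / 15.4 | 44.9% | 48.5% |
| 157 before 10% yearly loss | 141 / 127 | 14.0 / 14.65 | 49.2% | 53.1% |
| 140 analysed at both times | 140 / 140 | 14.0 / 14.0 | 48.9% | 57.2% |

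With the 6% yearly loss of the sampling section (157/1.06 = 148; 157/1.1236 = 140), the detectable increases are 13.7 and 14.0 pp and power is 51% and 57%. With all 157 per arm and no loss, the detectable increase is 13.3 pp.

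**Other methods at n = 140.** Unpooled variance gives 13.9 pp, the arcsine method 14.0 pp and a continuity correction 14.7 pp. Exact binomial power of the chi-square test for 10 pp is 49.2%.

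**What would give 10 pp at n = 140, changing one input at a time:**
- control suppression of about 85% instead of 70%;
- two-sided alpha of about 0.27;
- covariates explaining about half the variance: 1 − 140 × (0.10/2.802)²/0.37 = 0.52.

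The article states none of these. Two-sided alpha 0.10 alone gives 12.6 pp. Pooling the three incentive arms against control (420 vs 140) alone gives 11.5 pp.

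**The case against.** The best defence is that alpha is not stated and the suppression sentence names no contrast, while the Study design section frames the main goal as the GOALS intervention against standard care. With the incentive arms pooled, the gap shrinks: 11.5 pp at 420 vs 140, where power for 11 pp is 76%. If two-sided alpha 0.10 is assumed as well, starting from 157 per arm with 10% yearly loss, the result is 10.3 pp at month 12 and 10.8 pp at month 24, close to the printed figures. So the sponsor may have had inputs that work. However, that needs two departures from the usual reading, neither of them in the text, and the only contrast that the section names is between single arms. The result also could not be applied to arm-versus-control comparisons.

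Three stronger readings are tempting, and the documents do not support them:
- **The trial is too small.** Suppression is a secondary outcome. The chain from 560 to 628 to 1256 is built on adherence alone, and no recruitment number rests on 10 or 11 pp.
- **Power is as low as 41%.** That pairs the month-12 difference (10 pp) with the month-24 number (113). Matched by month, the lowest value is 45%.
- **The reference to three arms is a miscount that affects the calculation.** It may mean the three treatment arms. It is loose wording and changes no figure here.

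**Conclusion.** The stated detectable differences do not follow from the stated inputs. Per arm against control at two-sided 0.05, the detectable increase is about 14 to 15 pp. Power is about 45 to 49% for 10 pp at month 12 (51% under the 6% attrition figure) and 48 to 57% for 11 pp at month 24, against the 80% claimed.

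This rests on two assumptions, the alpha and the pairwise contrast. Relaxing either one alone does not rescue the figures. The error lies in a power statement for a secondary outcome; the design and the adherence-based sample size are not affected.

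A separate inconsistency bears on the same sentence. The power statement concerns binary suppression at months 12 and 24, the abstract names continuous log viral load, and the Outcomes section defines suppression at baseline and month 24 only. The month-12 power figure therefore has no matching defined outcome.

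**What to change.** In Sample size and power, do one of the following:
- restate the detectable increase in suppression as about 14 to 15 pp per arm versus control, giving alpha, the contrast and the number retained at each time point; or
- keep 10 and 11 pp and state the power as roughly 45 to 57%.

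If the printed figures came from a pooled contrast, a different alpha or a covariate gain, state that input and limit the claim to that analysis. Say whether 140 is before or after attrition, and which attrition rate applies. Clarify which three arms are meant.

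Separately, reconcile the abstract's viral-load outcome with the Outcomes section, so that the power statement refers to the defined outcome and time point.

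The cost is wording only, though the stated sensitivity becomes less favourable. Recruitment need not change.

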### Data analysis

Our primary analyses will be intention-to-treat analyses, with secondary analyses involving study completers only.

#### Estimating impact on primary outcomes

To estimate the impact of our interventions on primary outcomes, we will use an ordinary least squares Linear Probability Model. In the context of experimental evaluations, linear probability models provide unbiased estimates of program impact and correctly estimate standard errors (Gomila, 2020; Deke, 2014) [40, 41]. We will estimate an unadjusted model and a model that includes the following prespecified covariates to adjust for baseline characteristics and improve precision: age, education, sex, strata fixed effects, baseline WHO disease stage, baseline viral suppression, duration on ART, socioeconomic status as measured by the Poverty Probability Index for Uganda, and HIV disclosure status.

Mean adherence to ART and the fraction of clients with adherence of 90% or more will be analyzed with the following adjusted and unadjusted models:

Unadjusted:1$${y}_{it}={\beta }_{0}+{\beta }_{1}assigne{d}_{it}+{\beta }_{2}parti{c}_{it}+{\beta }_{3}fixe{d}_{it}+\overrightarrow{{\beta }_{4}}{\overrightarrow{S}}_{i}+{\epsilon }_{i}$$

Adjusted:2$${y}_{it}={\beta }_{0}+{\beta }_{1}assigne{d}_{it}+{\beta }_{2}parti{c}_{it}+{\beta }_{3}fixe{d}_{it}+\overrightarrow{{\beta }_{4}}{\overrightarrow{S}}_{i}+{X}_{it}\alpha +{\epsilon }_{i}$$$${y}_{it}$$ will be analyzed in two ways: as a continuous variable denoting mean adherence as the share of the prescribed bottle openings that were opened by individual $$i$$ on week $$t$$, and as a binary variable = 1 if the mean adherence exceeds 90% and = 0 if it is below 90%. In this model, the $${\beta }_{1}$$ represents the impact of assigned subgoals on the share of pills taken in a given week, $${\beta }_{2}$$ represents the impact of participatory subgoals on the share of pills taken in a given week and $${\beta }_{3}$$ represents the impact of fixed goals on the share of pills taken in a given week. $${\overrightarrow{S}}_{i}$$ represents strata fixed effects. Equation 3 includes the term $${X}_{it}$$, which represents the same covariates that are predictive of adherence.

The “Maintenance” and “Persistence” phases of the study will be analyzed for the number of months the participant spends in each phase. For the improvement phase, we will focus only on the month preceding month 12, as for that phase each participant in the participatory and assigned subgoals groups will display a different subgoaling path, and the only goal they share is to reach 90% adherence by month 12 (and eligibility for the prize drawing is measured for the 30 days preceding the month 12 visit).

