In this study, Goals for Adherence with Low-cost Incentives (GOALS), we will test two approaches to setting interim goals to test the relative contribution of subgoaling and ownership. It is well established in the psychology literature that goals mediate the effect of incentives on performance [36]. Yet evidence is lacking in terms of how to best set the eligibility goals in incentive interventions. GOALS proposes testing externally assigned subgoals (first treatment arm) and participatory subgoals (second treatment arm) with the goal to reach at least 90% adherence. The objective in year 1 is to identify the incentive design most effective for improving adherence. In addition to these interim prize drawings at regular clinic visits, there will be a larger prize drawing at month 12 to make achieving the 90% goal particularly salient. All treatment arms will receive weekly SMS motivational reminders with the goal of keeping incentives and their associated goals at the top of participants’ mind in the weeks between clinic visits. In year 2, the objective is to maintain adherence improvements and achieve viral suppression. Therefore, during the maintenance phase, incentive group participants will be required to remain 90% adherence, with a larger prize drawing for achieving viral suppression at the end of the maintenance phase. Most incentive studies measure behavior change over the short term (less than 6 months) [6]. By explicitly designing incentives to address the dual goals of improvement (year 1) and maintenance (year 2), we provide much-needed evidence on how to sustain adherence over time and prevent performance backsliding. GOALS will measure adherence for 6 months after the intervention ends to assess the impact of the different treatment arms on behavior change once incentives are withdrawn (persistence).

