The three treatment groups will receive weekly motivational messages and a reminder of their upcoming prize drawing. Weekly SMS messages will help maintain contact with study participants and enable them to become accustomed to receiving messages from the study for potential remote prize drawings (given the evolving COVID situation and corresponding clinic changes towards visits that are more spaced out, we expect some prize drawings to be done in person, and others remotely as further detailed below). In contrast, the control group will only receive the motivational portion of the text messages (without the reminders of the possibility of winning prizes) as an attention control due to the potential beneficial effects of text messages.

After the first year of the study, we will evaluate participants in the treatment groups to determine those who achieved high adherence of at least 90% (high adherers) and those who did not (low adherers).

Figure 1 below shows that in year 2, high adherers will progress to the “Maintenance phase” between months 12 and 24 where we will assess the intervention’s effectiveness in maintaining at least 90% adherence. They will have the chance to win prizes every 3 months if they maintain their adherence at or above 90% throughout this phase. They will then move to the “Persistence phase” between months 25 and 36 to assess the treatment arms’ impact on long-term adherence once incentives are removed.

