**Fig. 1 Fig1:**
[figure not shown]
Table showing different phases of the participants in different groups throughout the study

Low adherers will be given an additional 6 months in the “Improvement phase” between months 12 and 18. During this time, low adherers in the participatory subgoals group will have one more opportunity to set their personal target; they will be encouraged to set a target at month 15 such that they would achieve 90% by month 18. Low adherers in the assigned subgoals group will receive two more pre-chosen targets starting from their adherence at month 12 in equal increments up to 90% (e.g., if month 12 adherence is 80, their target is 85 for month 15 and 90 for month 18). The maintenance phase for the low adherers in the assigned goal and participatory goal groups will begin at month 18 for 12 months.

Low adherers in the fixed goal group will maintain their target of 90%. At month 18, we will identify the treatment arm with the highest effectiveness and move low adherence participants in the fixed goal arm to that arm to give them an opportunity to also benefit from the intervention. These participants will continue in the improvement phase between months 18 and 30, while assigned subgoals and participatory subgoals participants move to the maintenance phase. Low adherers across in the participatory and assigned goals group will complete their “Persistence phase” of the study in months 30–36.

All participants in the treatment groups will be eligible for a larger prize drawing at the end of their maintenance phase if they achieve viral suppression, defined as a viral load of 200 copies/mL or less.

Follow-up surveys will be conducted every 6 months for 24 months, and a cost-effectiveness analysis will also be performed after 36 months to help determine the intervention design’s potential for sustainability and scale-up.

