### Design

The study will use three intervention arms and a control arm. The intervention arms will all provide mobile airtime as incentives, but the incentives will be based on different eligibility criteria in the different arms. We will collect ART adherence data continuously for 3 months prior to the intervention, for 24 months after the intervention begins, and for 12 months after the intervention ends for all participants using Wisepill devices. We will acquire routine viral load measures for all participants throughout the study, which will be performed roughly every 12 months as per clinic and Uganda Ministry of Health guidelines. We will also conduct a baseline survey, and then surveys every 6 months for 24 months for all participants. See Fig. 2: SPIRIT figure for a detailed description of the timing of study activities.

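### Maintenance and persistence are analysed over windows set by each participant's own month-12 response, so year-2 and year-3 contrasts of the fixed-goal arm (T3) with control, T1 or T2 are not between randomised groups

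*Protocol article*

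**What the plan says.** **Analysis rule.** Estimating impact on primary outcomes states that the maintenance and persistence "phases of the study will be analyzed for the number of months the participant spends in each phase". The models in that section use weekly adherence, with control as the reference for the three arm coefficients.

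**Who gets which window.** Under Study design, after year 1, "we will evaluate participants in the treatment groups to determine those who achieved high adherence of at least 90" per cent. Only treatment-arm participants are classified. The text then gives:

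- High adherers: maintenance in months 12 to 24, then persistence "between months 25 and 36 to assess the treatment arms".
- T1/T2 low adherers: "The maintenance phase for the low adherers in the assigned goal and participatory goal groups will begin at month 18 for 12 months". They finish persistence "of the study in months 30–36".
- T3 low adherers: moved at month 18 to the arm judged most effective and kept in improvement until month 30. No maintenance or persistence window is stated.
- Control: no month-12 split and no phases in the text.

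**Statements pulling the other way.** Data analysis makes intention-to-treat primary. Sample size and power gives detectable differences at months 12 and 24 for each treatment arm against control and against each other.

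**Length of follow-up.** Background says "GOALS will measure adherence for 6 months after the intervention ends". Design says adherence is collected "for 12 months after the intervention ends for all participants using Wisepill devices".

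**The concern.** Month-12 adherence is a post-randomisation outcome that treatment may change. Once it decides who has an analysis window, and when, the sets being compared are no longer those that randomisation made alike. The effect is uneven across arms. T1 and T2 keep all their participants and only the timing and length of the windows vary. T3 keeps only those who were doing well at month 12.

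The later questions of the trial are at stake: whether adherence is maintained in year 2 and whether it persists once incentives stop. A fixed-goal arm represented by its responders would look good against control, T1 and T2 even if no arm had any effect.

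**Working it through.** **1. Windows side by side (from the text of Study design).**

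| Group | Maintenance | Persistence |
|---|---|---|
| High adherers, T1/T2/T3 | months 12–24 | months 25–36 (12 months) |
| Low adherers, T1/T2 | months 18–30 | months 30–36 (6 months) |
| Low adherers, T3 | none stated | none stated |
| Control | none stated | none stated |

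**2. Form of the bias with no treatment effect.** Let p be the share of high adherers and g the gap in later mean adherence between high and low adherers. An arm represented by its high adherers only is shifted from its full mean by (1 − p) × g. With p = 0.30 and g = 0.20 this is 0.70 × 0.20 = 14 pp. For p from 0.15 to 0.50 at the same gap it is 17 to 10 pp. Both p and g are assumptions.

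**3. Weighting in T1/T2 persistence.** High adherers supply 12 months and low adherers 6, so the high adherers' share of person-months is 12p / (12p + 6(1 − p)):

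- p = 0.15: 1.8 / 6.9 = 26%
- p = 0.30: 3.6 / 7.8 = 46%
- p = 0.50: 6 / 9 = 67%

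With p = 0.30 and g = 0.20, pooling weekly rows shifts the mean by (0.462 − 0.30) × 0.20 = 3.2 pp. Clustering standard errors by person, as planned, does not alter this weighting. One mean per person removes nearly all of it.

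**4. Null simulation.** The protocol gives no SD for adherence. Its 8 pp at 140 per arm and 80% power (two-sided 0.05 assumed) implies SD = 0.08 / [(1.960 + 0.842) × √(2/140)] = 0.239.

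Other inputs:

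- mean 0.62 (the protocol's control value) or 0.75 (assumed);
- between-person variance share 0.4, 0.6 or 0.8, and month-to-month autocorrelation 0.5 or 0.9 (all assumed);
- monthly adherence clipped to 0–1;
- high adherer means at least 0.90 in month 12;
- control assigned calendar months 13–24 and 25–36 (assumed).

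There was no treatment effect in any arm. About 12% were high adherers at mean 0.62, and 26 to 27% at 0.75. Ranges over the twelve settings:

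| Contrast, true value 0 | Maintenance | Persistence |
|---|---|---|
| T3 − control | +10.9 to +32.2 pp | +9.8 to +29.6 pp |
| T1 or T2 − control, weekly rows pooled | +0.1 to +0.9 pp | +1.5 to +4.2 pp |
| T1 or T2 − control, one mean per person | not separate (both windows 12 months) | 0.0 to +0.2 pp |

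Subtracting within settings gives T3 against T1 or T2. The smallest and largest maintenance values are 10.9 − 0.3 = 10.6 pp and 32.2 − 0.2 = 32.0 pp. For pooled persistence they are 9.8 − 2.0 = 7.8 pp and 29.6 − 3.2 = 26.4 pp.

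**5. Follow-up length.** For T1/T2 low adherers, maintenance ends at month 30. In a 36-month study that leaves 36 − 30 = 6 months, whereas 12 months would run to month 42. High adherers have 12 months. Neither the 6 months in Background nor the 12 months for all in Design fits both paths.

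**The case against.** - **Fig. 1 is not shown.** Its caption says that it sets out phases by group, so it may give control calendar phases and T3 low adherers a late window. This stands as a caveat. However, the text keeps T3 low adherers in improvement to month 30 of 36, which leaves at most six months, too few for a 12-month maintenance phase plus persistence. Treatment-arm windows would still depend on response where control windows would not.
- **Randomised comparisons are already present.** Intention-to-treat is primary, month 24 is powered between arms, and the improvement phase is judged in the month before month 12. All true. The month-12 comparison is unaffected. The defect is that the rule for the later phases is not reconciled with these statements.
- **A reader might infer that all later comparisons rest on self-selected subsets.** The text does not support this for T1 and T2: everyone there enters both phases, and T1 versus T2 is only mildly affected.
- **A reader might also infer that an arm converting more people will look worse, because it carries more marginal adherers into maintenance.** That would need an analysis restricted to high adherers, which no section prescribes. In T1 and T2 the non-converters enter as well.
- **A common-time analysis does not cleanly isolate the fixed goal or persistence.** This stands. T3 low adherers change scheme at month 18, and at month 36 time off incentives differs by path.

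**Conclusion.** The concern holds for contrasts of T3 with control, T1 or T2 in maintenance and persistence. On the visible text these set month-12 responders against whole arms, contrary to the intention-to-treat statement and the planned month-24 comparison between arms. The illustrative null bias for T3 minus control, about +10 to +32 pp, exceeds the 8 to 9 pp the trial is designed to detect. T1 and T2 against control are shifted by under 1 pp in maintenance, and by about 1.5 to 4 pp in persistence only if weekly rows are pooled.

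The sizes rest on an implied SD, assumed variance components and an assumed control window. That T3's responders-only mean is raised follows from selecting on an outcome correlated with later adherence, so it needs none of those figures. It does assume that Fig. 1 adds no window for T3 low adherers.

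**What to change.** 1. Make the year-2 and year-3 between-arm analyses intention-to-treat at common times since randomisation, for example the 30 days before months 24 and 36. Include everyone randomised: control, high adherers and low adherers.
2. State that T3 after month 18 is the assigned strategy including the planned move, and that at month 36 time off incentives differs by path.
3. Report results by phase as descriptive.
4. Reconcile the 12 months for all participants (Design) and the 6 months (Background) with the windows in Study design, which give 12 months for high adherers and 6 for T1/T2 low adherers. State the path for T3 low adherers.

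**Cost.** The protocol already plans electronic adherence monitoring in all arms, so this is analysis wording. It does change what is estimated: month 36 becomes a comparison of assigned strategies that mixes 12 and 6 months off incentives. The descriptive phase results can show that split, without randomised support.
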